## **3 INVESTIGATIONAL PLAN**

### **3.1 General Schema of Study Design**

This study is a randomized controlled trial. Please see Table 1 and Figure 1 for further descriptions of study design.

#### **3.1.1 Screening Phase and Initial Assessment**

All patients who present to the Children's Hospital of Philadelphia, Somerset Pediatric Group, JFK Institute, Rothman Orthopedic with a concussion date of injury 1-6 months ago will be screened for enrollment as case subjects using the protocol inclusion and exclusion criteria. Clinicians specializing in concussion management will identify potential subjects under their care in clinics after a standard clinical evaluation that consists of a detailed history and examination. A member of the study team will introduce the study to subjects deemed eligible to participate. Participants, or their legal guardians, will provide verbal consent to screening, and participants who are minors will provide verbal assent to screening, in person or over the telephone and will complete the majority of the screening process at the time of consent to screening. Those participants who pass the initial portion of the screening will be asked to complete the vision assessment portion of the screening in person. Eligible subjects will have time to ask questions and consider participation prior to consenting. Parental/guardian permission (informed consent) and, if applicable, child assent, will be obtained prior to any study related procedures being performed.

After consenting to participate, subjects will complete an initial optometric examination, vision assessments, and a patient-reported symptom questionnaire. The optometric examination will be completed by an optometrist. FMRI measurements will be conducted at the NJIT clinical site only.

#### **3.1.2 Study Treatment Phase**

Case subjects who enroll in the study will be randomized into two groups, one completing SCC+OBVAT and the other completing only SCC in phase 1. A member of the study team will assign subjects to one of the two arms using a pre-determined block randomization procedure. After randomization to a treatment arm, subjects will be provided with instructions on study procedures based on their treatment arm. Subjects in the SCC+OBVAT group (arm 1) will be contacted by a trained and certified vision therapist to schedule and complete their OBVAT sessions. The vision therapist will conduct all OBVAT sessions with participants and will instruct them on the in-home reinforcement. Subjects in both arms will

---

continue to follow-up with the physician treating their concussion as applicable. After the first 6 weeks and completion of outcome visit 1, subjects in the SCC only group (arm 2) will be contacted by a trained vision therapist to schedule and complete their OBVAT sessions.

### **3.2 Allocation to Treatment Groups and Blinding**

A member of the study team will randomize case subjects who consent to participate into one of the treatment groups at the conclusion of their initial assessment using a random number generator. Optometrists will be blinded to the treatment group.

### **3.3 Study Duration, Enrollment and Number of Sites**

#### **3.3.1 Duration of Subject Study Participation**

The study duration per subject will be up to 11 weeks  $\pm$  3 weeks for arm 1 and 17 weeks  $\pm$  3 weeks for arm 2. With up to 7 days screening, 6 weeks  $\pm$  2 weeks Phase 1, and up to 8 weeks  $\pm$  2 weeks Phase 2 for arm 2 and 2 weeks  $\pm$  1 week for Phase 2 arm 1.

### **3.4 Study Population**

#### **3.4.1 Inclusion Criteria (examples)**

#### **3.4.2 Index/Case Subject Inclusion Criteria**

- 1) Males or females age 11 to 35 years.
- 2) Best-corrected visual acuity of 20/25 in both eyes at distance and near.
- 3) Willingness to wear glasses or contacts to correct refractive error, if needed.
- 4) Global stereopsis of 500 sec of arc or better using Randot Stereo Test and local stereopsis of 70 sec of arc or better.
- 5) Symptomatic PPCS-CI defined as:
  - Near point of convergence (NPC)  $\geq 6\text{cm}$
  - Positive fusional vergence (PFV) at 40cm not meeting Sheard's criteria of at least twice the near phoria or a range of  $\leq 15\Delta$
  - CI symptom survey score (CISS) of  $\geq 21$  for adults and  $\geq 16$  for children
  - Diagnosis of a concussion from a clinician where symptoms persist for 1 to 6 months post injury
- 6) Parental/guardian permission (informed consent) and if appropriate, child assent.

#### **3.4.3 Index/Case Subject Exclusion Criteria**

- 1) Previous office or home-based vision therapy, orthoptics, home-based near-target push-ups, or pencil push-ups.
  - 2) Amblyopia or constant strabismus or strabismus surgery.
  - 3) High refractive error: Myopia  $\geq 6.0\text{D}$  sphere; Hyperopia  $\geq 5.0\text{D}$  sphere; Astigmatism  $\geq 4.0\text{D}$ ; Anisometropia  $> 1.5\text{D}$  difference between eyes; prior refractive surgery.
  - 4) Manifest or latent nystagmus evident clinically.
  - 5) Systemic diseases that affect accommodation, vergence or ocular motility (i.e. multiple sclerosis, Graves' thyroid disease, myasthenia gravis, diabetes, chemotherapy, or Parkinson's disease).
  - 6) Vertical heterophoria greater than  $1\Delta$ .
  - 7) Parents/guardians or subjects who, in the opinion of the Investigator, may be non-compliant with study schedules or procedures.
  - 8) Non-English speakers.
  - 9) For participants within the NJIT clinical site the additional exclusion criteria is necessary for fMRI imaging:
-

- A. Non-removable metal in the body.
- B. Subjects who are pregnant, planning on becoming pregnant during the study duration, or breastfeeding.
- C. Subjects who are metal workers.

Subjects that do not meet all of the enrollment criteria may not be enrolled. Any violations of these criteria must be reported in accordance with IRB Policies and Procedures.

## **4 STUDY PROCEDURES**

### **4.1 Screening Visit**

- Screening consent
- Screening interview
- Medical record review
- Vision exam
- Informed Consent/Assent/HIPAA authorization

### **4.2 Study Treatment Phase**

All subjects who are deemed eligible and interested in participating in the study after the screening will complete a written or electronic informed consent at their screening visit, before any study procedures take place. Subjects will then complete an initial assessment prior to the start of the treatment phase. The initial assessment may take place on the same day as the screening visit after informed consent has taken place.

For arm 1, the study treatment phase will consist of 12 one-hour OBVAT sessions bi-weekly followed by Outcome Visit 1. After completion of Outcome Visit 1, arm 1 subjects will complete 4 additional one-hour OBVAT sessions bi-weekly followed by Outcome Visit 2.

For arm 2, subjects will complete 6 weeks of SCC followed by Outcome Visit 1. After completion of Outcome Visit 1, arm 2 subjects will complete 16 one-hour sessions of OBVAT bi-weekly followed by Outcome Visit 2.

#### **4.2.1 Initial Assessment**

- Optometric Exam
-

- CISS-Con and VisQual-T (VisQual-T will be done both before and after objective eye movement testing)
- VRS3 objective eye movement test
- VET objective eye movement test

#### **4.2.2 fMRI (NJIT clinical site only)**

- Pregnancy test
- MRI anatomical scan, fMRI and arterial spin labeling (ASL)

#### **4.2.3 Between Initial Assessment and Outcome Visit 1 (Arm 1)**

- 12 one-hour bi-weekly OBVAT sessions
- Completion of at-home reinforcement (10-15 min sessions 3 times per week on the days not performing OBVAT while someone is enrolled in OBVAT)

#### **4.2.4 Between Initial Assessment and Outcome Visit 1 (Arm 2)**

- Standard-Community Concussion Care

#### **4.2.5 Outcome Visit 1**

- Clinical Optometric Exam and medical record review
- CISS-Con and VisQual-T (VisQual-T will be done both before and after objective eye movement testing)
- VRS3 objective eye movement test
- VET objective eye movement test
- MRI anatomical scan, fMRI, and ASL (NJIT clinical site only)

#### **4.2.6 Between Outcome Visits (Arm 1)**

- 4 one-hour bi-weekly OBVAT sessions
- Completion of at-home reinforcement (10-15 min sessions 3 times per week on the days not performing OBVAT while someone is enrolled in OBVAT)

#### **4.2.7 Between Outcome Visits (Arm 2)**

- 16 one-hour bi-weekly OBVAT sessions
  - Completion of at-home reinforcement (10-15 min sessions 3 times per week on the days not performing OBVAT while someone is enrolled in OBVAT)
-

#### **4.2.8 Outcome Visit 2**

- Clinical Optometric Exam and medical record review
- CISS-Con and VisQual-T (VisQual-T will be done both before and after objective eye movement testing)
- VRS3 objective eye movement test
- VET objective eye movement tests
- Anatomical, fMRI, and ASL (NJIT Clinical Site Only)\*

\*for arm 2 subjects only

#### **4.2.9 Outcome Visit 3 (NJIT clinical site only)**

- Clinical Optometric Exam and medical record review
- CISS-Con and VisQual-T (VisQual-T will be done both before and after objective eye movement testing)
- VRS3 objective eye movement test
- VET objective eye movement tests
- Anatomical, fMRI, and ASL

### **4.3 Subject Completion/Withdrawal**

Subjects may withdraw from the study at any time without prejudice to their care. They may also be discontinued from the study at the discretion of the Investigator for lack of adherence to study treatment or visit schedules. The Investigator or the Sponsor may also withdraw subjects who violate the study plan, or to protect the subject for reasons of safety or for administrative reasons. It will be documented whether or not each subject completes the clinical study. If the Investigator becomes aware of any serious, related adverse events after the subject completes or withdraws from the study, they will be recorded in the source documents and on the CRF.

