#### **4.3.1 Early Termination Study Visit**

Subjects will be withdrawn if their eligibility status changes such that it is no longer safe for them to complete the fMRI. If subjects choose to withdraw from the study, all of their longitudinal data will be excluded from the final data analysis. If initial baseline assessments are complete a group level comparison will be conducted with this current PPCS-CI data and the already collected TYP-CI and control data.

---

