    - **SCC only:** subjects assigned to the SCC only arm will be instructed to follow care instructions of their treating physician. SCC typically consists of physical and cognitive rest immediately following the injury for a brief period of time to allow symptoms to abate, followed by a gradual re-introduction of academic and physical activities, restricting activities at high risk for repeat brain injury (such as contact or collision sports) until a graded return to play protocol has been completed without provoking symptoms. For those patients who still have vestibular signs and symptoms persisting beyond 1-month post injury, initiation of vestibular and balance rehabilitation physical therapy (VBT) may occur, as determined by the physician with the goal of improving motion tolerance and balance through exercises that include adaption by retraining the vestibular ocular reflex. While some physical therapists incorporate pencil pushups or Brock string (common
-

treatments for CI) into their VBT protocols, they will be instructed specifically not to include any convergence exercises targeting CI.

- ***Home reinforcement:*** Subjects will be instructed on in-home reinforcement while they are completing their OBVAT intervention. The home reinforcement will utilize the HTS software. Subjects will be provided the HTS software in the form of a USB drive or a CD. HTS stimulates disparity convergence and sequences the therapy from ramp to step vergence demands, always providing immediate and accurate feedback to the patient, which has been shown to improve vision function. The HTS software also allows the investigator to monitor compliance and performance with the prescribed treatment by logging the number and time of sessions.

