#### **6.3.2 Efficacy Analysis**

The primary analysis will be based on an intention to treat approach and will include all subjects randomized at their initial assessment.

The primary efficacy endpoint will be the change in composite clinical parameters of near point of convergence and positive fusional vergence between the initial assessment and the outcome visits. A repeated measures ANOVA will be used to assess the clinical parameters as well as the chi-squared test using predetermined published optometric benchmarks for improvement.

Secondary endpoints will include the rate of symptom remediation in OBVAT+SCC group compared to SCC alone, change in vision function, and fMRI measures between the start and end of the treatment phase.

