## **7 STUDY INTERVENTION**

### **7.1 Description**

This study involves a therapeutic intervention testing the effect of OBVAT in adolescents and young adults with a PPCS-CI. Subjects will be randomly assigned to either SCC+OBVAT or SCC only arm using a random number generator. Subjects in the SCC+OBVAT arm will be asked to complete 12 one-hour biweekly OBVAT sessions in Phase 1 and an additional 4 one-hour biweekly OBVAT sessions in Phase 2. Subjects in the SCC only arm will be asked to follow SCC as instructed by their clinician for 6 weeks. Subjects will also be asked to complete at-home reinforcement during their OBVAT intervention.

All subjects will complete an optometric clinical exam, a self-reported symptom survey, fMRI and a suite of vision assessments at their study visits.

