#### **7.1.1 Treatment Compliance and Adherence**

Subjects must complete all of their OBVAT sessions and assessments to receive full compensation for participation in the study. Outcome visits will not be scheduled until the subject has completed all of their OBVAT sessions, and compensation will be dispensed upon completion of each outcome visit.

---

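### Section 4.3 lets investigators remove subjects from the study for poor adherence; before Outcome Visit 1 this exposes mainly arm 1 and undermines the intention-to-treat comparison

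*Protocol*

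**What the plan says.** Protocol section 4.3 gives the Investigator an exit rule: "They may also be discontinued from the study at the discretion of the Investigator for lack of adherence to study treatment or visit schedules". The sentence after it lets the Investigator or Sponsor withdraw anyone who departs from the study plan, and also gives safety and administrative grounds. The exit is from the study, not only from treatment. No adherence threshold is set.

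Before Outcome Visit 1 the two arms are asked to do different things. Arm 1 has "12 one-hour bi-weekly OBVAT sessions" (section 4.2.3) plus home software sessions three times a week. Arm 2 has "Standard-Community Concussion Care" (section 4.2.4). Section 7.1 puts it this way: "Subjects in the SCC only arm will be asked to follow SCC as instructed by their clinician for 6 weeks".

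On adherence data, section 5.1.3 says: "The HTS software also allows the investigator to monitor compliance and performance with the prescribed treatment by logging the number and time of sessions". That software is used only while a subject is receiving OBVAT.

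The analysis statement in section 6.3.2 is: "The primary analysis will be based on an intention to treat approach and will include all subjects randomized at their initial assessment". Two other rules bear on it. Section 7.1.1 says: "Outcome visits will not be scheduled until the subject has completed all of their OBVAT sessions". Section 4.3.1 says: "If subjects choose to withdraw from the study, all of their longitudinal data will be excluded from the final data analysis".

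**The concern.** Arm 1 against arm 2 at Outcome Visit 1 is the randomised comparison of OBVAT plus standard care with standard care alone. An intention-to-treat analysis of it needs outcomes on everyone randomised, whatever they did afterwards. Section 4.3 allows staff to end a subject's participation because of behaviour after randomisation. That behaviour has much more scope to show itself in arm 1, where there are study sessions to miss and a log that records missed home work.

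The rule can also be applied with knowledge of the arm. Sections 3.2 and 9.1.2 describe blinding for the optometrists only, and section 9.1.1 has the study team tracking each subject's assigned group.

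If subjects who adhere poorly also tend to improve less, the arm 1 subjects who reach Outcome Visit 1 are a selected group and arm 2 is not selected to the same degree. A statistical analysis plan can say how to handle missing outcomes. It cannot recover measurements that the protocol allowed staff to stop taking.

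**Working it through.** **1. Are removed subjects followed up?** Section 4.3 ends participation and says only that related serious adverse events that come to light later are recorded. Section 4.3.1 is headed as an early termination visit but lists no assessments. No other section keeps a subject discontinued for non-adherence in outcome assessment.

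**2. How unequal is the exposure?** Over the nominal six weeks, arm 1 has 12 office sessions and 3 x 6 = 18 home sessions, so 12 + 18 = 30 scheduled study-treatment tasks. Arm 2 has no study sessions and no software log. Arm 2 is not free of exposure, however. It has a visit schedule to keep, it can depart from the study plan (for example by doing convergence exercises in vestibular therapy, which section 5.1.3 rules out), and medical record review in section 5.1.1 collects notes on compliance with therapies.

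**3. What size of bias could follow?** The protocol has no figure to reproduce here. It gives neither the share likely to be removed nor any link between adherence and outcome. Its only retention figure is the 80% assumed in section 6.4, which covers all causes. The inputs below are therefore assumptions:

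- no true treatment effect;
- adherence and outcome bivariate normal with correlation ρ;
- the least adherent fraction q removed from arm 1 and nobody removed from arm 2 (the extreme case);
- unit SD in both arms;
- n = 75 per arm (150/2) or 50 per arm (section 6.4).

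Bias in SD units: b = ρ x φ(z_q) / (1 - q).

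Type I error of a two-sided 0.05 z-test: 1 - Φ(1.96 - b/SE) + Φ(-1.96 - b/SE), with SE = √[1/(n(1 - q)) + 1/n].

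Example with q = 20%, ρ = 0.3, n = 75: φ(z_q) = 0.280, so b = 0.3 x 0.280/0.8 = 0.105. SE = √(1/60 + 1/75) = 0.173, and the type I error is 0.093.

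| q | ρ | Bias (SD) | Type I error, 75 per arm | Type I error, 50 per arm |
|---|---|---|---|---|
| 5% | 0.1 | 0.011 | 0.050 | 0.050 |
| 5% | 0.3 | 0.033 | 0.054 | 0.053 |
| 5% | 0.5 | 0.054 | 0.062 | 0.058 |
| 10% | 0.1 | 0.019 | 0.052 | 0.051 |
| 10% | 0.3 | 0.058 | 0.064 | 0.059 |
| 10% | 0.5 | 0.097 | 0.089 | 0.076 |
| 20% | 0.1 | 0.035 | 0.055 | 0.053 |
| 20% | 0.3 | 0.105 | 0.093 | 0.078 |
| 20% | 0.5 | 0.175 | 0.173 | 0.131 |

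**4. Cross-check by a simpler route.** If a fraction p of arm 1 is removed and would have improved d SD less than those who stay, the arm 1 mean rises by m - [(1 - p)m + p(m - d)] = p x d. With p of 10-20% and d of 0.5-1 SD (assumed), that runs from 0.10 x 0.5 = 0.05 to 0.20 x 1 = 0.20 SD, which is the same order.

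**5. After the fix.** With nobody removed (q = 0), the bias from this source is 0 and the type I error is 0.05.

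**The case against.** Four arguments on the other side carry weight.

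- **One-sidedness.** A reader might infer that poor adherers are removed from arm 1 alone. The text does not say so. Removal is a discretion and not a requirement, and the visit-schedule and study-plan grounds reach arm 2. The exposure is unequal, not confined to one arm, so the table shows the extreme case.
- **Contradiction with intention to treat.** A reader might infer that section 4.3 flatly contradicts section 6.3.2. It does not. Section 4.3 is about participation and says nothing about dropping data, and the exclusion in section 4.3.1 is worded for subjects who choose to leave. What section 4.3 does is create missing outcomes, which undermines the stated analysis.
- **Direction.** A reader might infer that the bias must inflate OBVAT. That is plausible: sections 9.4.2 and 9.4.4 expect that therapy may provoke symptoms, which could reduce attendance. But subjects who recover early may also stop attending, and removing them would work the other way.
- **Added effect.** As written, section 7.1.1 already denies Outcome Visit 1 to an arm 1 subject who has not finished the sessions, so section 4.3 may add little loss at present. That stands, and it is why the passages must be corrected together. Correcting section 7.1.1 alone would leave the discretion in section 4.3 intact.

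The size is also open to challenge. Losing 20% of arm 1 through this rule would by itself use up the whole loss implied by 80% retention, and at a correlation of 0.1 the type I error is at most 0.055.

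**Conclusion.** The point holds as a weakness in the conduct rules that should be corrected. Section 4.3 does not separate stopping treatment from leaving the study for subjects who adhere poorly. It sets no criterion, and before Outcome Visit 1 it exposes arm 1 more than arm 2. The outcomes lost this way would be missing because of events after randomisation, potentially at different rates by arm.

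Under the assumed ranges (5-20% removed from arm 1 only, correlation 0.1-0.5) the spurious difference is about 0.01-0.18 SD. The type I error is then 0.050-0.173 at 75 per arm and 0.050-0.131 at 50 per arm. The lower end is negligible and the upper end is not. How often the discretion would be used is unknown, so neither the size nor the direction can be settled from the protocol.

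**What to change.** In section 4.3, delete non-adherence and violation of the study plan as grounds for discontinuing a subject from the study, and record both as deviations. State that a subject who stops or does not complete OBVAT, for whatever reason, is still invited to the already planned outcome visits at their scheduled times and is analysed in the arm assigned, unless consent is withdrawn.

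Leave in place the safety and administrative grounds in section 4.3 and the fMRI-safety rule in section 4.3.1. Then reconcile section 4.3 with sections 4.3.1, 6.3.2 and 7.1.1. In particular, section 7.1.1 now withholds outcome visits until every OBVAT session is done, so an invitation in section 4.3 would have no effect while that sentence stands.

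The change alters no treatment rule. Section 6.5 already treats ending OBVAT as a step of its own, and section 3.4.3 already screens out expected non-compliers before randomisation. The cost is wording in a few sections. Staff must invite poor adherers to visits already planned, and the estimated effect may be somewhat smaller because those subjects are included.

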#### **4.3.1 Early Termination Study Visit**

Subjects will be withdrawn if their eligibility status changes such that it is no longer safe for them to complete the fMRI. If subjects choose to withdraw from the study, all of their longitudinal data will be excluded from the final data analysis. If initial baseline assessments are complete a group level comparison will be conducted with this current PPCS-CI data and the already collected TYP-CI and control data.

---

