**Site Principal Investigator**

**[name]**

Salus University, Pennsylvania College of Optometry

[name]

[name]

[contact]

Email: [[contact]](mailto:[contact])

**Overview:** **Convergence Insufficiency in Post-Concussive Symptoms study is funded via the NIH R01 EY023261.** Currently, the protocol described below is approved by CHOP IRB where NJIT and Rutgers have agreed to have CHOP be the IRB of record. The original CHOP proposal will be submitted for reference with the following modifications.

**Proposed modifications from original IRB:** NJIT is the primary institution funded via the NIH and hence it would be better for NJIT to be the lead institution for IRB. To facilitate recruitment, another clinical site (The Eye Institute of Salus University) has been added. Thus, there are the following three clinical sites: NJIT, CHOP and Salus. Drs. [name] and [name] will recruit for the NJIT clinical site. [name] will recruit for the CHOP clinical site and [name] will recruit for the Salus clinical site. FMRI parameters will only be conducted at the NJIT clinical site. A one-year follow-up assessment will only be conducted for the NJIT clinical site.

---

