### **5.1.3 Other Evaluations, Measures**

- **Clinical Examination:** A standard optometric clinical exam that includes near point of convergence, positive fusional vergence, dissociated phoria, corrected visual acuity, unilateral cover test, stereopsis, monocular amplitude of accommodation, accommodative facility, vergence facility at near and far, negative fusion vergence, and eye movement and vestibular evaluation will be performed by a practicing, licensed optometrist.
  - **Patient-Reported Outcome Surveys:**
-

- CISS-Con
  - Vision Quality of Life with Time Survey (VisQual-T)
  - **VET:** An ISCAN eye tracker integrated into an Oculus head mounted display DK2 will track and record subjects' eye movement. The VET is about a 20 minute protocol comparing vergence steps at the beginning and end of a test while performing vergence steps and ramps, and saccades.
  - **VRS3:** An ISCAN eye tracker integrated into an Oculus head mounted display DK2 will track and record subjects' eye movement. The VRS3 is about a 15 minute protocol of vergence ramps, vergence steps, and saccades objective eye movements.
  - **Intervention:** This study involves a therapeutic intervention testing the effect of OBVAT in adolescent and young adults with PPCS-CI. Subjects will be randomly assigned to either an SCC+OBVAT or SCC only group using a pre-determined block randomization procedure.
    - **SCC+OBVAT:** subjects assigned to the SCC+OBVAT arm will attend bi-weekly OBVAT sessions with a trained and certified vision therapist. OBVAT has four phases. The first phase will be designed to manage some of the visual/vestibular issues common in PPCS-CI using eye movements associated with head and body movement. In phase 2, techniques will be used to stimulate gross convergence, positive fusional vergence and monocular accommodative therapy using Brock string, Vectograms, Computer Orthoptics and Lens Accommodative Rock, respectively. Once the subject can perform these tasks with ease, s/he will graduate to the third phase which is ramp fusional vergence and monocular accommodative therapy with Vectograms, Aperture Rule, Lifesaver Cards and Lens Accommodative Rock. The final stage will consist of jump fusional vergence and binocular accommodative facility. The initial phase is used to remediate vestibular issues if present but if there are no vestibular issues, then this phase will be omitted.

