## **5.2 Efficacy Evaluations**

### **5.2.1 Diagnostic Tests, Scales, Measures, etc.**

Subjects will complete an optometric examination, vision assessments, fMRI (NJIT clinical site only) and symptom report at all assessment visits (except arm 1 will not perform an fMRI at the second outcome). Data obtained from these assessments will be tracked and compared between the start and end of the treatment phase for all case subjects enrolled in the study, regardless of treatment arm.

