## **6 STATISTICAL CONSIDERATIONS**

### **6.1 Primary Endpoint**

The primary endpoint will be the change in composite clinical parameters of near point of convergence and positive fusional vergence between the initial assessment and the outcome visits.

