### **6.2 Secondary Endpoints**

Secondary endpoints will include the rate of symptom remediation in OBVAT+SCC group compared to SCC alone, change in vision function, and fMRI measures over the duration of the intervention.

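### Section 4.3.1 withdraws a subject from the study when fMRI becomes unsafe, so later clinical outcomes that need no scanner are lost at the NJIT site (minor)

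*Protocol*

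**What the plan says.** Section 4.3.1, under the heading on subject completion and withdrawal, reads: "Subjects will be withdrawn if their eligibility status changes such that it is no longer safe for them to complete the fMRI". The instruction is mandatory and offers no alternative in which only the scan is omitted.

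Imaging is confined to one of three clinical sites. The opening overview says "FMRI parameters will only be conducted at the NJIT clinical site". Section 3.4.3 introduces the pregnancy and metal exclusions with "For participants within the NJIT clinical site the additional exclusion criteria is necessary for fMRI imaging". At that site the scan is also not part of every visit: under section 5.2.1, all assessments occur at every visit "except arm 1 will not perform an fMRI at the second outcome".

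The primary endpoint in section 6.1 is clinical: "The primary endpoint will be the change in composite clinical parameters of near point of convergence and positive fusional vergence". Its source is described in section 5.1.3: "A standard optometric clinical exam that includes near point of convergence, positive fusional vergence, dissociated phoria". Imaging appears in section 6.2 among the secondary endpoints: "change in vision function, and fMRI measures over the duration of the intervention".

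Section 6.3.2 defines the analysis population: "The primary analysis will be based on an intention to treat approach and will include all subjects randomized at their initial assessment".

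**The concern.** Section 4.3.1 turns a condition for entering the scanner into a condition for staying in the trial. A randomised NJIT subject who becomes pregnant or acquires non-removable metal leaves the study, even if willing to attend the remaining visits. The clinical outcomes at those visits could have been measured without any imaging.

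An intention-to-treat analysis of all randomised subjects depends on outcomes being sought from all of them. Outcomes that the protocol stops collecting cannot be recovered later, whatever the statistical analysis plan says about missing data. The conflict therefore lies in the protocol itself. What is at stake is avoidable missing data at one site; loss of power is secondary.

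**Working it through.** **1. Does any clinical outcome need the scanner?** Sections 5.1.3 and 4.2.5 to 4.2.9 give the source of each.

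| Outcome | Source | Scanner needed |
|---|---|---|
| NPC, PFV (primary, 6.1) | optometric examination | no |
| CISS-Con, VisQual-T | questionnaires | no |
| VRS3, VET | head-mounted eye tracker | no |
| fMRI measures (secondary, 6.2) | MRI at NJIT only | yes |

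The protocol already collects the first three rows without imaging: at CHOP and Salus throughout, and at NJIT for arm 1 at Outcome Visit 2.

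**2. Can eligibility change after randomisation?** Yes. Section 5.1.2 re-screens for MRI contraindications before each scan. Table 1 repeats the NJIT pregnancy test at visits 2, 3 and 4, with randomisation at visit 2. The visit 4 test is not restricted by arm, although the visit 4 scan is for arm 2 only. An arm 1 subject could thus be found ineligible for fMRI at a visit where no scan is due.

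**3. How many subjects?** Section 3.3.2 plans 30-50 subjects at CHOP, 30-50 at Salus and 50-75 at the NJIT site.

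- NJIT share: 50/110 = 45%; 75/175 = 43%.
- The protocol gives no rate of new MRI ineligibility. Assumed range: 2% to 10%.
- Expected number = NJIT subjects × rate. Low: 50 × 0.02 = 1. High: 75 × 0.10 = 7.5, or about 8.
- Share of 150 evaluable subjects: 1/150 = 0.7%; 7.5/150 = 5.0%.

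**4. What does it cost in power?** The sample sizes in section 6.4 (37, 6, 37 and 46) cannot be reproduced, because standard deviations are given without mean differences. I therefore take its 80% power as the starting point. Section 6.4 allows for 80% retention and 15% loss to motion artefact (0.80 × 0.85 = 0.68). It names no separate allowance for fMRI-safety withdrawals, so these would have to come out of the 20% non-retention.

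I use a two-arm comparison of means, normal approximation, two-sided 0.05, with the loss split equally between arms. If power is 80% at n per arm and n′ remain, then power = Φ[(1.960 + 0.842) × √(n′/n) − 1.960].

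| n per arm | Total lost | n′ per arm | Power |
|---|---|---|---|
| 75 (150 subjects, 1:1) | 1 | 74.5 | 79.7% |
| 75 | 7.5 | 71.25 | 78.0% |
| 50 (section 6.4) | 1 | 49.5 | 79.6% |
| 50 | 7.5 | 46.25 | 76.9% |

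For the third worst-case step at 75 per arm: √(71.25/75) = 0.9747; 2.802 × 0.9747 − 1.960 = 0.771; Φ(0.771) = 0.780. The largest loss is about 2 points at 75 per arm and about 3 points at 50 per arm. If only the scans stop, this rule costs the clinical outcomes nothing.

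**The case against.** The strongest defence is that imaging is not incidental to this trial. Section 2.1 makes neural mechanism the primary objective (although the abstract and synopsis give that place to treatment effectiveness), and the fMRI beta weight set the sample size, at 46 per arm. MRI contraindication is already a full exclusion at NJIT, so section 4.3.1 extends a choice made at entry. This stands as an explanation: the rule has a reason. But the reason accounts for a missing scan. It does not require clinical follow-up to end after randomisation.

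The effect is also small. Subjects planning pregnancy are excluded at NJIT, the first scan falls at the randomisation visit, and a retention allowance exists. This too stands and sets the grade.

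A reader might infer four stronger things that the protocol does not support:

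- **Differential loss by arm.** Arm 2 stays longer and has a scan at Outcome Visit 2. But the controlled contrast of OBVAT plus SCC against SCC alone lies at Outcome Visit 1. Up to then both arms have the same 6 ± 2 weeks and the same scans. The extra arm 2 exposure comes after that arm has also started OBVAT.
- **Reach to CHOP and Salus.** The sentence names no site, but subjects there have no fMRI to complete and no fMRI eligibility to lose.
- **Deletion of data already collected.** Section 4.3.1 excludes longitudinal data only for subjects who themselves choose to leave. For subjects withdrawn over fMRI safety, the certain loss is of later visits; the handling of earlier data is not stated.
- **A leftover from a design with imaging at all sites.** Section 7.1 still has all subjects completing fMRI, and section 5.3 still refers to MRI under CHOP policy. This makes the history plausible, but it is an inference.

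**Conclusion.** The point holds in a narrow form and is minor. At the NJIT site, section 4.3.1 ends study participation for a reason that concerns imaging only. It thereby stops collection of later clinical outcomes in randomised subjects who may be willing to continue, against section 6.3.2.

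The size rests on an assumed rate of 2-10%, for which the protocol offers no figure, applied to 50-75 subjects. The power figures also assume that the planned 80% holds at the outset and that losses fall equally on the arms. The decision not to scan is not in question. The conclusion rests on avoidable missing data and the internal conflict; the power loss alone would not justify raising it.

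**What to change.** Reconcile sections 4.3.1 and 6.3.2 on outcome collection. Suggested wording for 4.3.1:

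*An NJIT subject for whom fMRI is no longer safe will have no further fMRI. With the subject's consent, non-imaging outcome assessments will continue to be collected at the remaining outcome visits and will be analysed in the randomised arm. Only the fMRI endpoints will be treated as missing.*

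The wording should cover outcome collection only. Whether study treatment continues after such a change stays with the treating clinicians and the existing safety provisions.

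The cost is one short protocol amendment, with no added visits, staff or subjects. The downside is a few subjects with clinical data but no later fMRI data.
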